### 7.2 Data Transfer

Newly entered clinical center data are received by the coordinating center immediately upon data entry. The coordinating center merges newly received data with the accumulated data in a SAS database.

### 7.3 Central Data Management System

After the first level of editing, data transferred from the clinical centers are imported into the official study SAS database on the Biostatistics Center's IBM 390 enterprise server. The coordinating center performs quality control checks on the data (see below), querying the clinical center regarding data issues and adding corrections to the central database.

### 7.4 Quality Control

Range checks, inter-item checks, cross-table checks, and double data entry verification are used where appropriate to ensure accurate data entry. Specific quality control procedures are run to check for missing, incorrect, and questionable values immediately after they are entered. Reports with the necessary patient identifying information and the problem values are printed and sent to the clinical centers for correction. When returned, corrected values are entered and checked again for consistency with other items. The goals are to make quality control a continuous process, to make the turnaround time between error detection and correction as short as possible, and to document any changes made to the database.

## 7.5 Backup, Data Security, and Confidentiality

The Biostatistics Center's data backup and security policies ensure the safety and confidentiality of the data. Backup procedures include: twice-weekly system backup, daily incremental backup, and off-site fire proof storage. Security procedures include: logon and link password protection, remote password logon and dial-back modems, and for internet access, separate Web servers which use SSL and encryption algorithms. Regularly updated virus scanning software is used routinely to check personal computers for computer viruses. University computing facilities provide support in the event of a disaster.

The coordinating center maintains confidentiality of patient data and emerging results per a confidentiality policy, which every staff member is required to sign annually.

## 7.6 Tracking Study Progress

The purpose of tracking reports is to keep the collaborative group informed of study progress, and to report special problems and resolutions. Reports are produced regularly by the coordinating center, as directed by the Steering Committee. These reports are distributed to the study group through the study website.

Tracking reports include the following types of information:

- screening and enrollment (versus goal), by clinical center, gender, and race/ethnicity
- tables describing adherence to the study protocol (attendance at scheduled study visits, study intervention compliance)
- database inventory
- number of data edit queries generated and outstanding, by clinical center
- characteristics of the patient population, by clinical center
- progress of analysis and manuscripts

## 7.7 Archival and Study Close-out

At the end of the study, after all data have been received and edited, the database is archived in computer readable format, including: readme documentation files, text files of study documents (forms annotated with variable names, protocols, and manuals of procedures), data files in the form of SAS transport files and input statements, data dictionaries, and program code documenting primary derived variables.

After the results have been published, all data will be available to other investigators. Data will be stored at a readily accessible site.

# 8 Statistical Considerations

## 8.1 Sample Size

The primary outcome for the TODAY study is time to treatment failure, defined as persistently elevated HbA1c levels ( $\geq 8.0\%$  for 6 months) or the inability to be weaned safely from temporary use of insulin therapy. No published data exist that allow estimation of the rate of occurrence. From unpublished data collected in the participating clinical centers, it is estimated that between 10-20% of children will have an HbA1c above the threshold by the end of each 6 month period, beginning at the end of the first year. The following assumptions were used to determine the sample size goal for TODAY:

- Primary outcome is time to failure as defined above.
- Eligible patients are randomized evenly to one of three treatment arms and followed for an additional two years following close of randomization.
- Rate of treatment failure within treatment group is constant over time.
- Treatment failure in the reference group (metformin alone) is at least 10% per six-month period, beginning at the first annual visit.
- There is a reduction of at least 40-50% in the treatment failure rate in one of the more intensively treated groups.
- Ten percent of patients are lost to drop-out during each 6 month period.
- The type I error rate ( $\alpha$ ) is 0.05 (two-sided) with a Bonferroni adjustment [Miller 1981] for three pair-wise comparisons of the three treatment groups.

Given these assumptions, if 10% of the metformin group has an HbA1c above the threshold, 250 participants per arm provides at least 90% power to detect a 50% reduction in the treatment failure rates in at least one combination therapy group (i.e., 5% with HbA1c above threshold during a six-month period). If 20% of the metformin group has an HbA1c above the threshold, 250 participants per treatment arm provides at least 90% power to detect a 40% reduction in hazard rates in at least one of the combination therapy groups (i.e., 12% failing during a six-month period). Therefore, 250 participants per group are recruited.

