## 2 Outcomes and Objectives

### 2.1 Primary

The primary objective of the TODAY trial is to compare the three treatment arms on time to treatment failure in patients enrolled from 10 to 17 years of age with T2DM. The study is analyzed as an 'intention to treat' study enrolling 750 patients (250 per arm). The study is powered to allow all three possible comparisons between the treatment groups while maintaining the overall significance level at 0.05. The three treatment group comparisons are: (1) metformin alone versus metformin plus intensive lifestyle program, (2) metformin alone versus metformin plus rosiglitazone, and (3) metformin plus intensive lifestyle program versus metformin plus rosiglitazone. Treatment failure is defined in one of two ways:

1. **HbA1c  $\geq$  8% over a 6-month period.** All regularly scheduled HbA1c values must be  $\geq$  8% over a 6-month period. If any one value is  $<$  8%, after which HbA1c re-elevates to  $\geq$  8%, the clock will restart at the time of the re-elevation. At least two consecutive measurements must be  $\geq$  8% over 6 months.
2. **Inability to wean from temporary insulin therapy due to metabolic decompensation.** Participants who experience metabolic decompensation requiring temporary use of insulin, who cannot safely be weaned from insulin within three months, will be classified as treatment failures (see section 4.7).

The primary outcome of treatment failure is defined in terms of HbA1c, because it correlates with glycemic control and long-term diabetes outcome. Because HbA1c is the primary outcome, investigators and patients are blinded to HbA1c values. In addition, patients with abnormal reticulocyte count or HbA1c chromatogram indicating the presence of abnormal hemoglobin variants other than heterozygosity for S and C at the time of initial screening are excluded from participation due to interference with HbA1c assays. Homozygous S and C and S/C patients are excluded. These patients are referred for appropriate hematologic evaluation. Management of patients with metabolic decompensation requires insulin treatment. However, if insulin treatment cannot be withdrawn after three months, this is considered a failure of the primary therapy.

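### Shaffer's step-down would gain power over the flat Bonferroni split for the second and third pairwise conclusions, at the same overall 5% level and the same sample size

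*Protocol*

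**What the plan says.** Section 2.1 makes all three pairwise contrasts primary: "The study is powered to allow all three possible comparisons between the treatment groups while maintaining the overall significance level at 0.05". Section 8.1 lists, among the assumptions behind the sample size, a type I error rate of "0.05 (two-sided) with a Bonferroni adjustment" "for three pair-wise comparisons of the three treatment groups". It then makes two power statements: "250 participants per arm provides at least 90% power to detect a 50% reduction in the treatment failure rates" when 10% of the metformin arm fails per six months, and "250 participants per treatment arm provides at least 90% power to detect a 40% reduction in hazard rates" when 20% does. Both refer to at least one of the two combination arms.

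Section 8.2 sets an overall 0.05 for the primary outcome and an O'Brien-Fleming-type Lan-DeMets spending function for interim looks. Its sentence on significance levels is incomplete in the text available, which is not a fault of the plan. In the readable text, Bonferroni is the only rule for multiplicity between arms.

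**The concern.** Three pairwise nulls among three arms are logically linked, and a flat Bonferroni split ignores the link. If arms 1 and 2 differ, arm 3 cannot equal both. After one true rejection, at most one null is therefore left to protect, yet a flat split still holds each remaining test to 0.0167.

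The second and third conclusions are at stake: whether both combinations beat metformin, and whether lifestyle and rosiglitazone differ. Section 2.1 asks for them, while the power statements in section 8.1 cover only at least one combination arm.

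**Working it through.** **Inputs.** 250 per arm (section 2.1); equal allocation (section 8.1: "Eligible patients are randomized evenly to one of three treatment arms"); constant failure rates (section 8.1: "Rate of treatment failure within treatment group is constant over time"); failures beginning at the first annual visit; 10% drop-out per six months; two years of follow-up after the close of randomization (all section 8.1). Accrual is three years (section 1.2), taken here as uniform. Section 3.1 says four years; the conclusion does not depend on which is used.

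**The plan's own figure.** The Bonferroni level is 0.05/3 = 0.0167, critical |z| = 2.394. On the exponential scale, 10% against 5% gives HR = ln 0.95 / ln 0.90 = 0.487, and 20% against 12% gives HR = ln 0.88 / ln 0.80 = 0.573. Schoenfeld events for 90% power are 4(2.394 + 1.282)²/(ln HR)², which gives 105 and 175. Power by the same formula:

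| Setting | 10% v 5% | 20% v 12% |
|---|---|---|
| Risk from entry, 3-year accrual | 97.6% | 98.1% |
| Risk from entry, 2 years of follow-up only | 91.4% | 94.7% |
| Risk from year 1, 3-year accrual | 88.0% | 91.0% |

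The stated 90% is broadly reproduced at 0.0167; the lowest value is 2 points short.

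**Why Shaffer's rule is valid.** Consider how many of the three nulls are true.
- All three: an error needs the smallest p to be at or below 0.05/3, with probability at most 3 × 0.05/3 = 0.05.
- Exactly two: impossible, because two equalities imply the third.
- Exactly one: an error needs that null's p to be at or below 0.05, with probability at most 0.05.
- None: no error can occur.

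The first step is the same as Bonferroni's and the later steps are more lenient, so no Bonferroni rejection is lost.

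**Expected events, risk from year 1.** With λ = −2 ln(1 − p) and μ = −2 ln 0.9 = 0.2107 per year, time at risk after year 1 is uniform on 1 to 4 years. Events = 250 · e^(−μ) · λ/(λ+μ) · (1 − m), where m = [e^(−(λ+μ)) − e^(−4(λ+μ))]/[3(λ+μ)].
- 10%: 250 × 0.81 × 0.5 × 0.6276 = 63.5
- 5%: 250 × 0.81 × 0.3274 × 0.5261 = 34.9
- 20% and 12%, by the same formula: 106.4 and 73.5

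Check for 10% against 5%: SE = √(1/63.5 + 1/34.9) = 0.2107; |ln HR|/SE = 0.7197/0.2107 = 3.416; 3.416 − 2.394 = 1.022, so power is 84.7%. This variance is larger than Schoenfeld's because events are unequal, hence 85% here against 88.0% above. Both rules below use the same variance.

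**Comparison of the rules.** 500,000 simulated sets of three arm-level log-hazard estimates (variance 1/events), a single final look, risk from year 1:

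| Rates (metformin/A/B) | Quantity | Bonferroni | Shaffer |
|---|---|---|---|
| 10/5/5% | Each comparison with metformin | 84.6% | 90.6% |
| | Both comparisons with metformin | 74.0% | 85.9% |
| | At least one of three pairs | 95.2% | 95.2% |
| 20/12/12% | Each comparison with metformin | 90.0% | 94.4% |
| | Both comparisons with metformin | 82.7% | 91.5% |
| | At least one of three pairs | 97.3% | 97.3% |
| 10/5/10% | Effective arm v metformin | 84.7% | 89.7% |
| 10/5/7.5% (illustrative) | Metformin v the 7.5% arm | 21.3% | 34.5% |
| | 5% arm v 7.5% arm | 30.8% | 46.3% |
| All equal | Family-wise error | 4.4% | 4.4% |
| Exactly one true null | Family-wise error | 1.7% | 5.0% |

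In no replicate did Bonferroni reject where Shaffer did not. With risk from entry the gains shrink, because power is already high: both comparisons with metformin go from 93.5% to 97.5% at 10/5/5% and from 96.0% to 98.6% at 20/12/12%.

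**The case against.** The strongest reply is that Bonferroni appears only as a sample-size assumption. Sizing on a conservative level does not bind the analysis to it, section 8.2 nowhere says each pair is tested at 0.0167, and the order of pairwise tests is commonly left to an SAP, which is not shown. That stands as a limit: a reader might infer that the final analysis is fixed at 0.0167 per pair, and the protocol does not say so outright. It does name this adjustment and no other, so the point concerns a stated choice, not a missing one.

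Other stronger readings also fail.
- **Alpha or N is wrong.** Bonferroni is valid and the stated power is broadly met with it.
- **The trial is more likely to find something under Shaffer.** The first step is still 0.0167, so the chance of at least one rejection is identical. The power target in section 8.1, at least one combination arm, gains essentially nothing.
- **Bonferroni buys nothing.** With exactly one true null its family-wise error is 1.7% against 5.0%, and it has matching simultaneous intervals. Shaffer's extra power comes from that slack.
- **Any closed test dominates Bonferroni.** A closed test gated by a 2-df logrank does not. Bonferroni needs z² = 2.394² = 5.73, the global gate 5.99, and Bonferroni alone rejected in up to 0.35% of replicates.

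It is also fair that the interim looks complicate the rule. The step-down remains valid by closure when the spending function is applied at each step's level, but the power and error figures above are for one look.

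**Conclusion.** This is an efficiency point that holds: a cheap improvement, not a correction of an error. At the protocol's planned effects, with risk from the first annual visit, Shaffer adds about 4 to 6 points to each comparison with metformin and 9 to 12 points to showing both. For smaller contrasts the gain is about 13 to 16 points, but the 10/5/7.5% rates behind that figure are illustrative and not planned in the protocol. If risk starts at entry, the gain for showing both falls to about 3 to 4 points. Validity and containment of the Bonferroni rejections are exact. The power figures rest on constant hazards, uniform three-year accrual, a normal approximation and a single look.

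**What to change.** State the primary testing rule in section 8.2, and refer to it from section 8.1: order the three pairwise p-values; test the smallest at 0.05/3; if it is rejected, test the other two each at 0.05; otherwise stop. Apply the O'Brien-Fleming-type spending function at the level of the step concerned (0.05/3, then 0.05) at every interim and final look. If the SAP already names a sharper rule, align the protocol with it. Settle the rule before anyone choosing it sees comparative results. Keep 250 per arm.

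The cost is a short passage of wording and a second set of monitoring boundaries, with no extra patients or visits. Simultaneous confidence intervals will not match the step-down exactly, so say which intervals will be reported. The family-wise error with exactly one true null uses the full 5%.

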## 8.2 Statistical Analysis

The principal analyses of primary and secondary outcomes employ the "intent-to-treat" approach [Peduzzi et al. 1993]. The intent-to-treat analyses include all randomized patients with all patients included in their randomly assigned treatment group; treatment group assignment is not altered based on the patient's adherence to the assigned treatment regimen. All statistical tests are two-sided with the overall significance level of the primary outcome  $\alpha$

$\alpha = 0.05$ . However, b

TODAY, the significance levels used in the interim and final analyses of the primary outcome are adjusted to account for the multiplicity of interim analyses.

- *Baseline characteristics:* Comparison of the baseline characteristics among the three treatment groups uses standard nonparametric statistical techniques, such as Fisher's exact test for categorical data and the Kruskal-Wallis test for ordinal or continuous data.
- *Primary outcome:* The principal analysis of TODAY is an analysis of the time to treatment failure. Turnbull's [1976] algorithm is used to calculate and compare Peto's [1973] nonparametric estimates of the interval-censored survival curves for each treatment group. For the primary outcome analysis, patients are considered "administratively censored" if they complete the full duration of TODAY without having failed. Patients who prematurely discontinue their follow-up visits without having reached study endpoint are "censored" as of their last follow-up visit. Failure is considered to have occurred during the interval between the last HbA1c value  $< 8\%$  and the first HbA1c value used to classify the participant as a treatment failure.
- *Secondary outcomes:* Secondary time to "event" outcomes (e.g., cardiovascular risk factors, microvascular outcomes) are analyzed using the same life-table methods described above for the primary outcome. A proportional-hazards regression model is used to evaluate potential covariates that may modify the primary and secondary time to

event outcomes (e.g., risk population defined by race/ethnicity, age, clinical site). Graphical procedures are used to assess the proportionality assumption. If the proportionality assumption is found to be unreasonable, then other models such as the accelerated failure time model [Wei 1992] or the proportional odds model [McCullagh 1980] are used to evaluate the covariates.

Life-table analysis assesses the risk of the first event in time. Some processes, however, involve recurrent events such as the back-and-forth between elevated and normal blood pressure. For these recurrent events, the family of statistical models based on the theory of counting processes are applied [Fleming and Harrington 1991].

Longitudinal data analysis techniques are used to analyze repeated measures data (e.g., glycemia, fasting lipids, blood pressure, physical activity, quality of life). These include: (1) analyses of the point prevalence of a discrete characteristic (e.g., hypertension) at successive repeated visits over time [Lachin and Wei 1988]; (2) multivariate rank analyses of quantitative (e.g., 2 hour OGTT) or ordinal (e.g., the Child Health Questionnaire subscales) measures over successive visits [Wei and Lachin 1984]; (3) the parametric linear random effects model of Laird and Ware [1982] to compare participant slopes over time (e.g., rate of change in fasting glucose) under linearity and normality assumptions; and (4) techniques developed by Liang and Zeger [1986] to compare participant slopes under a generalized linear models framework.

- *Interim analysis:* The Lan-DeMets [1983] spending function approach is used to adjust the probability of a type I error for testing the primary outcome when interim ‘looks’ of the data are taken by the Data Safety Monitoring Board. The spending function corresponding to an O’Brien and Fleming [1979] boundary are used. The Lan-DeMets procedure is flexible, in that the number of looks does not have to be specified in advance and the time interval between looks does not have to be the same throughout TODAY. The rate at which the type I error is spent is a function of the fraction of total information available at the time of the interim analysis (i.e., information time). For an interim analysis using the logrank test (i.e., time to confirmed treatment failure), the information time is the fraction of the total number of confirmed treatment failures to be accrued in the entire TODAY. Since the total number of failures to be accrued is unknown, an estimate of the information time is based on the fraction of total patient exposure [Lan and Lachin 1990].

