- *Temporary use of insulin:* Some patients may require temporary suspension of study drug and use of insulin. This is referred to as 'on leave' and may be due to (1) temporary medical conditions such as hospitalization or intercurrent illness (see chapter on safety), (2) a sexually active female not on appropriate contraception, or (3) pregnancy (see section on pregnancy below). While 'on leave', patients and clinicians remain masked to study drug and TLP activities are modified as needed by the intervention team. The patient continues to attend quarterly visits but HbA1c outcome measurement is discontinued during temporary use of insulin, except during pregnancy and nursing when A1c is measured for clinical care. Any case in which the participant has been on temporary insulin therapy for  $\geq 2$  weeks must be reviewed by the Protocol Review Committee. If the participant has been off study medications for  $\geq 1$  month, study procedures associated with an annual visit are not collected until the patient is back on study treatment (drug and/or TLP) for an adequate time period.  
Any type or dose of insulin can be used at the discretion of the treatment team. In such cases, an attempt is made to withdraw insulin once the acute event has resolved and study drugs are resumed. In the case of pregnancy, participants are weaned over a 3 month period once pregnancy and lactation are complete. In the case of a temporary medical condition such as hospitalization or intercurrent illness, weaning occurs over 2 weeks if the event lasted 2 weeks or less; if the event lasted more than 2 weeks, weaning occurs over 1 month. Withdrawal of insulin occurs regardless of blood glucose values; if metabolic decompensation occurs, appropriate safety procedures are followed (see next bullet for details).
- *Metabolic decompensation:* Metabolic decompensation is defined as hyperglycemia (BG > 300 mg/dL) accompanied by significant symptoms (e.g., vomiting, dehydration, lethargy) and/or moderate or large urinary ketones, or sustained hyperglycemia during home glucose monitoring [80% of BG tests are > 300 mg/dL (non-fasting) or > 200

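### HbA1c failures are back-dated to the first elevated value but non-failures are censored at the last visit, so the primary failure curves come out too low; the treatment contrast is affected only if dropout differs by arm

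*Protocol*

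**What the plan says.** Three statements in the protocol have to be read together.

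- **Definition (section 2.1).** On the HbA1c route every scheduled value over six months must be at or above 8%; "At least two consecutive measurements must be" at that level. On the insulin route, participants "who cannot safely be weaned from insulin within three months, will be classified as treatment failures".
- **Event date (section 8.2, primary outcome).** "Failure is considered to have occurred during the interval between the last HbA1c value" below 8% "and the first HbA1c value used to classify the participant as a treatment failure". The right-hand end of the interval is the start of the qualifying run, about six months before the failure could be recognised.
- **Censoring date (section 8.2, primary outcome).** "Patients who prematurely discontinue their follow-up visits without having reached study endpoint are" censored "as of their last follow-up visit". Those who finish the trial without failing are censored administratively at its end.

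Nothing in the protocol moves the censoring date back, or treats an elevation not yet confirmed at the last visit as undetermined.

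**The concern.** The event date uses data collected up to six months later; the censoring date does not. Take two participants whose HbA1c first reaches 8% at month 30 and stays there. One is followed to month 36 and becomes a failure dated at about month 30. The other has a last visit at month 33 and enters the analysis as known to be failure-free to month 33. The second record claims something nobody established.

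The Turnbull estimator does not repair this, because it takes the censoring times it is given as verified failure-free time. Nor is dropout needed: end-of-study censoring produces the same gap.

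At stake are the absolute failure curves of the primary outcome in every arm and, if retention differs between arms, the comparison itself.

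**Working it through.** **Inputs.** Failure 10% (alternative 20%) per six months, dropout 10% per six months, 250 per arm, two-sided 0.05/3 = 0.0167 per comparison (section 8.1); three-year accrual and at least two years of follow-up (section 1.2; section 3.1 says four years of recruitment); visits every two months in year 1, then every three months (sections 5.1 and 6.2.2). Assumptions added: crossings start at month 6, elevation persists once it starts, and dropout is unrelated to HbA1c.

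**1. The plan's own figure.** Hazard ratios are ln(0.95)/ln(0.90) = 0.487 and ln(0.88)/ln(0.80) = 0.573. Exponential failure and dropout with the Schoenfeld formula at 0.0167 give power 0.944 and 0.957 with failures from month 6 (0.976 and 0.981 from month 0; 0.880 and 0.910 from month 12). The stated power of at least 90% is broadly reproduced, so the inputs are being read as intended.

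**2. True curve.** With crossings from month 6, months 24/36/48 hold 3/5/7 six-month periods at risk: 1 − 0.9³ = 27.1%, 1 − 0.9⁵ = 41.0%, 1 − 0.9⁷ = 52.2%.

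**3. What the rule loses.** A crossing counts only if the participant is still followed about six months later. Away from study end, that has probability 1 − d, where d is six-month dropout. The counted hazard is therefore roughly (1 − d) times the true hazard. With d = 0.10: 0.9 × (−ln 0.9) = 0.0948 per period, so over three periods 1 − exp(−0.2845) = 24.8% against 27.1%. Administrative censoring, and uncounted crossers who stay in the risk set, lower it further.

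**4. Simulation on the protocol's visit grid** (400,000 participants; product-limit curve on grid visits as a stand-in for Turnbull):

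| Cumulative failure | 24 mo | 36 mo | 48 mo |
|---|---|---|---|
| True, 10% per 6 months | 27.1% | 41.0% | 52.2% |
| Protocol rule | 23.7% | 34.0% | 41.2% |
| Onset dating, censoring stepped back | 27.2% | 41.1% | 52.3% |
| True, 20% per 6 months (1 − 0.8³, 1 − 0.8⁵, 1 − 0.8⁷) | 48.8% | 67.2% | 79.0% |
| Protocol rule | 43.1% | 58.0% | 66.9% |

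At 10% and 10%, about 6% of randomized participants, one fifth of all observed crossings, are elevated but unconfirmed when censored. With no dropout at all, and crossings allowed from month 0, the four-year figure is still 50% against a true 57%.

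**5. Between-arm effect with equal true failure rates.** From step 3 the apparent hazard ratio should be close to the ratio of six-month retention, (1 − d₂)/(1 − d₁). At a 10% failure rate:

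| Dropout per 6 months | Retention ratio | Simulated HR, protocol rule | Type I error (nominal 0.0167) |
|---|---|---|---|
| 10% vs 10% | 1.00 | 1.00 | about 0.02 |
| 8% vs 12% | 0.88/0.92 = 0.96 | 0.95 | about 0.02 |
| 5% vs 15% | 0.85/0.95 = 0.89 | 0.89 | about 0.04 |

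Stepped-back censoring and confirmation dating both give HR 1.00 in all three rows, with type I error of about 0.02, nominal within simulation error. With equal dropout, a true HR of about 0.49 stays at 0.49 under the protocol rule.

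**The case against.** The strongest reply is that the trial exists to compare arms, and section 8.1 plans a single dropout rate for all patients. Under that assumption the comparison is sound: HR 1.00 under the null, the planned effect preserved, type I error the same under every dating rule. Administrative censoring falls on randomized arms alike. This stands, and it limits the certain damage to the absolute curves.

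It is tempting to go further in four ways, none of which the protocol supports.

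- **That the lifestyle arm will look better because it will lose more patients.** No arm-specific dropout is given. TLP sessions are weekly only in months 1–6 and then thin out (section 4.4.4), and attrition is monitored (section 5.3). A split of 5% vs 15% is severe: 1 − 0.95⁸ = 34% against 1 − 0.85⁸ = 73% lost by 48 months. At 8% vs 12% the effect on error is slight.
- **That everyone's last six months are event-free.** The insulin-weaning route has a three-month window, so this is true only of the HbA1c route.
- **That interim and final tests run on different time scales.** The phrase "For an interim analysis using the logrank test (i.e., time to confirmed treatment failure") may mean only that unconfirmed failures are not counted; it states no event date. Information time is estimated from patient exposure, which does not depend on how failures are dated.
- **That weaning failures cannot be dated at all.** "HbA1c outcome measurement is discontinued during temporary use of insulin", with exceptions, so the HbA1c rule fits this route poorly. But section 2.1 fixes the three-month point, and a dating convention for the second route is a detail an analysis plan may supply.

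A fair point also concerns the remedies: neither helps if patients leave because their HbA1c is rising.

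**Conclusion.** The rule as written gives a wrong primary failure curve. Under the plan's own rates, cumulative failure is understated by about 3, 7 and 11 percentage points at 24, 36 and 48 months (27.1 − 23.7, 41.0 − 34.0, 52.2 − 41.2). That rests on three-year accrual, crossings from month 6, persistent elevation, and a grid-based stand-in for the Turnbull estimator.

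The bias in the treatment contrast is conditional. It is absent with equal dropout, small at 8% vs 12% per six months, and material at 5% vs 15%, where type I error is a little over twice nominal. These unequal rates are assumptions chosen around the planned 10%.

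The inconsistency lies in dating and censoring rules that the protocol fixes itself, so it should be corrected there and not left to the analysis plan.

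**What to change.** Adopt one of two rules in section 8.2.

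1. **Keep onset dating.** Censor every non-failure at the last HbA1c visit that has a complete six-month confirmation window after it. This keeps the present meaning of the endpoint.
2. **Date failure at confirmation.** Use the visit that completes the six-month run, or the date of the three-month weaning failure, and censor at the last HbA1c visit. This estimates time to confirmed failure and moves reported times about six months later.

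Under either rule, state that the same event date applies at interim and final analyses. The same participants count as failures; only the analysis times change.

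The cost is wording and programming, with no new data and no change to patient care. Both rules remove the bias when dropout is unrelated to HbA1c. Neither corrects for participants who leave because their HbA1c is rising, so the report should say that this remains.
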